### Sample Size and Data Analysis

Based on the Pharmacist Identification of New, Diagnostically Confirmed OA (PhIND-OA) study [22,37], 40% of residents from British Columbia in Canada (N=194, mean age=62 years) started to exercise after receiving an OA diagnosis and minimal intervention (ie, a pamphlet and the self-management program). We expect that, if OPEN is efficacious, 60% of the intervention group will meet or exceed the recommended level of physical activity at follow-up. Taking into account a 15% loss to attrition over 6 months, 80% power to detect a difference of 20% in physical activity rates between groups and alpha level of .05, a total of 252 participants (126 per group) will be needed. To validate the self-reported physical activity measure, the MLTPAQ, a subsample of 40 participants will be recruited. Assuming we observe a Pearson correlation of .5 for MLTPAQ and VO_2Peak_, a 95% confidence interval around the estimate would range from 0.26 to 0.74.

As the aim of a proof-of-concept study is to demonstrate evidence of efficacy, a per-protocol analysis will be performed. For the primary outcome, dichotomized physical activity participation (ie, yes/no to meeting the American College of Sports Medicine recommendation) from baseline to 3 and 6 months will be analyzed in a logistic regression model after adjusting for the baseline measurement, age, and sex. Intention-to-treat analysis will assess the robustness of the findings. Analysis of covariance (ANCOVA) will analyze the difference in KOOS scores (overall and subscales) between the groups over time. No adjustment will be made for multiple comparisons because Type II error is a greater concern than Type I error in proof-of-concept studies [56,57].

We will examine the mechanisms of OPEN on physical activity participation by conducting mediation analysis using the bootstrapped sampling distribution model by Preacher and Hayes [58,59]. Changes in TPB variables over the intervention period (ie, between baseline and 3 months) will be examined as potential mediators on physical activity behavior at 3 months. In addition, changes in TPB variables over the entire study period (ie, baseline to 6 months) will be examined as potential mediators on physical activity participation at 6 months. Finally, an exploratory analysis using Pearson’s correlations will examine the association between MLTPAQ (ie, energy expenditure) and the VO_2Peak_.

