Secondary outcomes will be measured with the Knee Injury & OA Outcome Score (KOOS) [49,50]. The KOOS consists of 5 subscales: knee pain, stiffness, daily activity, sports/recreation, and quality of life. It was originally developed for people recovering from injuries such as anterior cruciate ligament and meniscus injury, and has been validated in people with OA [49,50]. KOOS includes all items of the Western Ontario MacMaster OA Index (WOMAC) in its original format [51] and has a normalized aggregate score ranging from 0 (worst outcome) to 100 (best outcome). Motivation for physical activity will be measured with Rhodes’s 7-point Likert-type TPB questionnaire [52-54]. It consists of 16 items measuring all components of the TPB model, including behavioral, normative, and control beliefs. Previous studies using this measure have shown good predictive validity and internal consistency in adult populations [52-54]. Demographic variables and comorbid conditions will also be collected at baseline. Website statistics (frequency and duration of use, intervention group only) and adverse events (falls, cardiovascular, and musculoskeletal events) [55] will be tracked monthly.

Finally, in a convenient subsample of participants (n=20 per arm), we will perform an aerobic fitness test at baseline, 3 months, and 6 months. Aerobic fitness tests (VO_2Peak_) will be conducted by an assessor who is blinded to the group assignment. Heart rate, blood pressure, and VO_2_ will be recorded at rest, during each exercise stage, and in recovery.

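### The planned 95% confidence interval for the MLTPAQ–VO2peak correlation (0.26 to 0.74) rests on a symmetric approximation; the Fisher z interval for r = 0.5 and n = 40 is 0.22 to 0.70

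*Protocol article*

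**What the plan says.** The section *Sample Size and Data Analysis* of the protocol article states that, to validate the self-reported activity measure, "a subsample of 40 participants will be recruited". Its precision is then illustrated: "Assuming we observe a Pearson correlation of .5 for MLTPAQ and VO_2Peak", "a 95% confidence interval around the estimate would range from 0.26 to 0.74". No interval method is named.

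The same section describes the analysis itself: "an exploratory analysis using Pearson’s correlations will examine the association between MLTPAQ (ie, energy expenditure) and the VO_2Peak". It does not say which visit the correlation uses. The section *Randomized Controlled Trial* says of the subsample that "we will perform an aerobic fitness test at baseline, 3 months, and 6 months".

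The attrition allowance, "Taking into account a 15% loss to attrition over 6 months", appears only in the calculation for the 252 participants of the main trial.

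**The concern.** A correlation cannot exceed 1, so when it is well away from zero its sampling distribution is skewed. An interval with equal arms around 0.5 (0.24 on each side) therefore suggests that the skewness was ignored. At n = 40 this can matter in the second decimal place.

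The interval is the only quantitative support given for a subsample of 40. The goals listed at the end of the Introduction include, as the third secondary goal, the agreement between self-reported exercise and a performance-based measure, and the MLTPAQ is also the instrument for the primary outcome. In a validation analysis the reader looks mainly at the lower limit, because it shows how weak the true correlation could still be. If that limit is set too high, the planned evidence looks slightly stronger than it is.

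**Working it through.** **Inputs** (all from *Sample Size and Data Analysis*): r = 0.5; n = 40; 95% level, taken as two-sided, so z = 1.96. The 15% attrition is used only in step 4.

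**1. Reproducing the stated figure.** The Wald interval is r ± 1.96 × (1 − r²)/√(n − k), where the divisor varies between textbooks. Here 1 − r² = 0.75.

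| k | Interval | Rounded |
|---|---|---|
| 0 | 0.268 to 0.732 | 0.27 to 0.73 |
| 1 | 0.265 to 0.735 | 0.26 to 0.74 |
| 2 | 0.262 to 0.738 | 0.26 to 0.74 |
| 3 | 0.258 to 0.742 | 0.26 to 0.74 |

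(For k = 1 the unrounded limits are 0.2646 and 0.7354.) The stated interval is thus a Wald interval with k = 1, 2 or 3. Two alternatives do not match: the standard error √((1 − r²)/(n − 2)) gives 0.225 to 0.775, and a one-sided z with the Wald standard error gives about 0.30 to 0.70.

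**2. Fisher z interval on the same inputs.** The formula is tanh(atanh(r) ± 1.96/√(n − 3)).

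- atanh(0.5) = 0.5493
- 1/√37 = 0.1644, and 1.96 × 0.1644 = 0.3222
- limits on the z scale: 0.2271 and 0.8715
- back-transformed: 0.223 and 0.702

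The lower limit differs from the stated one by 0.26 − 0.223 = 0.037 and the upper by 0.74 − 0.702 = 0.038. The widths are 0.74 − 0.26 = 0.48 and 0.702 − 0.223 = 0.479.

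**3. Which interval earns the 95% label.** Simulation with bivariate normal data, true correlation 0.5, n = 40, 100,000 runs, Wald form with k = 1:

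- Coverage was 92.6% for Wald and 95.0% for Fisher z.
- A second simulation of the same size split the misses. The Wald interval lay wholly above the true value in 5.7% of runs and wholly below it in 1.5%, against 2.5% nominal on each side. Fisher z missed in 2.7% and 2.2%.

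The Wald form therefore falls short by about two percentage points, and it errs mostly by excluding true correlations weaker than the one observed.

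**4. Conditional case: a 6-month correlation.** If the 15% loss is assumed for the subsample, 40 × 0.85 = 34 remain. Then 1.96/√31 = 0.3520, and the Fisher z limits are tanh(0.5493 ± 0.3520) = 0.195 and 0.717, which is 0.19 to 0.72 from the unrounded 0.1948 and 0.7169. The width is 0.52. A baseline correlation could use all 40, and step 2 would apply.

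**The case against.** The strongest defence is that the figure follows from the document's own inputs by a recognised formula. No method is named, so nothing in the article contradicts it, and the sentence serves to show the precision that 40 people would give. That precision, measured by width, is the same under either method. All of this stands: the point concerns the choice of approximation and where the interval sits, and there is no slip of calculation. The defence does not rescue the 95% label, which the Wald form does not deliver at this sample size.

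Several stronger readings are tempting, and the documents do not support them:

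- *The subsample is too small.* With Fisher z, a lower limit of 0.26 at r = 0.5 would need about 51 people. However, the article sets no threshold, null value or decision rule for this correlation, so a lower limit of 0.22 in place of 0.26 changes no planned conclusion. The limit is clear of zero either way.
- *Attrition was wrongly left out.* The 15% is stated for the main sample only, and the visit used for the correlation is not given. The figure for 34 people is therefore a scenario and does not show an omission.
- *Precision within one arm is what counts.* The article describes one subsample of 40 and plans no correlation by arm.

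Nor does the article say that the Wald form will be applied to the data. The interval is a planning illustration.

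**Conclusion.** The point holds as a minor correction. For r = 0.5 and n = 40 the interval should read 0.22 to 0.70. The stated limits are each about 0.04 too high, the width is essentially right, and the method behind them covers about 93% with the excess error on the optimistic side.

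The coverage figures assume bivariate normal data and a true correlation of 0.5. The interval of 0.19 to 0.72 rests on two further assumptions: that the correlation is taken at 6 months, and that the subsample loses 15%.

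The analysis is labelled exploratory. Neither the primary comparison nor the 252 participants depend on it.

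**What to change.** Replace the sentence with: *Assuming r = .5, the 95% CI (Fisher z) would be 0.22 to 0.70 with 40 participants.* Use Fisher z intervals when the correlation is reported. If a 6-month correlation is intended, say so and add that the interval would be 0.19 to 0.72 if 34 complete.

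The cost is one sentence. Design, recruitment and data collection stay as they are, and the stated width at 40 participants does not worsen.

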To develop a behavioral theory-informed Internet intervention for people with early knee OA.To assess the efficacy of OPEN through a proof-of-concept randomized controlled trial (RCT). The *primary goal* of this ongoing RCT was to determine if OPEN could increase participation in physical activity in people with previously undiagnosed, early knee OA at 6 months. We hypothesized that the Internet intervention plus an information pamphlet about OA would improve participation in physical activities in persons with early OA, compared to those who would receive only the pamphlet (ie, controls). Our *secondary goals* were to assess: (1) whether the intervention has an effect on knee pain, stiffness, and physical function at 6 months, (2) whether differences between groups could be explained through a mediation model based on a behavioral theory (ie, the TPB), and (3) in a subsample of participants, the agreement between self-reported exercise behaviors and a performance-based measure of physical activity.

Guided by Graham’s Knowledge-to-Action process [41], this study will directly address a key recommendation from the 2005 Summit on Standards for Arthritis Prevention and Care:

Every Canadian must be informed about the importance of achieving and maintaining a healthy body weight, and actively encouraged to engage in physical activity to prevent the onset and worsening of arthritis. [42]

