The intervention group will receive an emailed password. Participants will receive an automatically generated email prompt to access the website every 2 weeks, with a short newsletter about the ongoing projects at ARC, for the first 3 months. The website will remain accessible throughout the study, but no further prompting emails will be sent after 3 months. In addition, they will receive, by email, an education pamphlet. It will contain information about OA, physical activity, and other treatments.

The control group will receive the same pamphlet by email. For the first 3 months, participants will also receive the same newsletter about the ongoing projects at ARC every 2 weeks by email. During the intervention period, both groups will be able to contact a physical therapist for a consultation via email if they experience increased discomfort after activities.

Outcome measures will be administered online at baseline, 3 months, and 6 months. The primary outcome will be the proportion of participants to meet the American College of Sports Medicine physical activity recommendation of 150 minutes or more of weekly physical activity (moderate or heavy intensity) at 6 months, as measured using the modified Minnesota Leisure Time Physical Activity Questionnaire (MLTPAQ). The MLTPAQ assesses the frequency and amount of time spent on 63 activities in 8 categories: walking, conditioning exercise, water activities, winter activities, sports, garden activities, home repair activities, fishing, and hunting. The average time spent on moderate and heavy physical activity and average weekly energy expenditure (kilocalories/week) will be calculated using the standardized intensity code associated with each activity [44]. It has shown test-retest reliability in both men and women (*r*=.79-.82) [45] and has been validated against caloric intake and treadmill tests [46-48].

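### The primary analysis of a superiority trial is per-protocol, with intention-to-treat kept as a robustness check, so the headline comparison is not protected by randomisation

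*Protocol article*

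**What the plan says.** All references are to the Methods of the protocol article unless stated.

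- **Analysis set.** Sample Size and Data Analysis says "As the aim of a proof-of-concept study is to demonstrate evidence of efficacy, a per-protocol analysis will be performed". The primary-outcome model follows directly: logistic regression of meeting the activity recommendation, adjusted for baseline measurement, age and sex. Then: "Intention-to-treat analysis will assess the robustness of the findings". Per-protocol is therefore the main analysis and intention-to-treat the secondary one.
- **Hypothesis.** At the end of the Introduction, OPEN plus pamphlet is expected to be better: it "would improve participation in physical activities in persons with early OA, compared to those who would receive only the pamphlet (ie, controls").
- **Adherence data.** Randomized Controlled Trial lists "Website statistics (frequency and duration of use, intervention group only") among the items tracked monthly. Of the comparator it says "The control group will receive the same pamphlet by email". Controls also get the newsletter, and no measure of their use of either is described.
- **Sample size.** The planning rates are 40% for control and, for OPEN, "60% of the intervention group will meet or exceed the recommended level of physical activity at follow-up". The only allowance for losses is "Taking into account a 15% loss to attrition over 6 months", giving 252 in total, 126 per group.

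**The concern.** A per-protocol set is chosen by what happens after randomisation. In a superiority comparison, the groups left after that choice are no longer the groups that were randomised, and a difference between them may reflect who was kept as well as what OPEN does. An interest in efficacy can justify estimating the effect in users. It does not make a comparison of selected subsets a randomised one.

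Two features of this trial give the risk a direction. First, adherence can be observed in one arm only, so a usage rule could remove OPEN participants but no controls. Second, the Introduction names lack of motivation as a barrier to activity and reports that intention and perceived control explain about 30% of the variance in activity. Low website users are plausibly the less motivated, and removing them would raise the OPEN rate without any treatment effect. The primary model does not adjust for motivation.

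At stake is the conclusion itself. The Discussion would use a positive result to support implementing lifestyle interventions, which calls for the effect of offering OPEN to everyone allocated to it. If the two analyses disagree, the plan makes the per-protocol result the headline.

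**Working it through.** **1. Reproduce the stated sample size.** Inputs from Sample Size and Data Analysis: p1 = 0.40, p2 = 0.60, alpha 0.05, power 80%, attrition 15%. Sidedness is not stated; two-sided reproduces the figure.

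- Uncorrected n per arm = [1.960·√(2·0.5·0.5) + 0.8416·√(0.24 + 0.24)]² / 0.20² = 96.9, so 97.
- With continuity correction: (96.9/4)·[1 + √(1 + 4/(96.9·0.20))]² = 106.7, so 107.
- With attrition: 107/0.85 = 125.9, so 126 per arm and 252 in total. This matches exactly.

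Without the correction the result would be 97/0.85, so 115 per arm (230). At 107 per arm the power is 80.1% with continuity correction and 83.8% without. The stated power is right for a set that loses only the 15%.

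**2. Bias if membership depends on website use (assumed inputs).** The article gives no exclusion rate and no activity rate among low users, so both are assumed. Suppose OPEN has no effect, 40% are active in both arms, there are 107 completers per arm, and a share e of OPEN completers is excluded, of whom a share q are active.

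Rate among those kept = (0.40 − e·q)/(1 − e).

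For e = 0.20 and q = 0.20: (0.40 − 0.04)/0.80 = 0.45, a spurious gain of 5 points. The number kept is 107·0.80 = 85.6. The pooled rate is (107·0.40 + 85.6·0.45)/192.6 = 0.422, and the standard error is √[0.422·0.578·(1/107 + 1/85.6)] = 0.0716. The chance of rejection is Φ((0.05 − 1.960·0.0716)/0.0716) = 10.4%, plus 0.4% in the other tail, about 11%.

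| e | q | Spurious gain | Rejection, uncorrected |
|---|---|---|---|
| 0.20 | 0.40 | 0 | 5% |
| 0.20 | 0.30 | 2.5 points | 6% |
| 0.20 | 0.20 | 5 points | 11% |
| 0.30 | 0.20 | 8.6 points | 21% |

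With continuity correction the last two rows become about 8% and 17%. The first row is the no-bias case. These are unadjusted two-proportion approximations to the planned logistic model.

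**3. Exclusions beyond attrition and the power statement.** With the effect held at 60% v 40%, and further exclusions from OPEN only:

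| Excluded from OPEN | Power, corrected | Power, uncorrected |
|---|---|---|
| 0% | 80.1% | 83.8% |
| 10% | 77.7% | 81.8% |
| 20% | 74.8% | 79.3% |
| 30% | 71.1% | 76.1% |

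On the basis that reproduces 252 there is no slack. This table assumes that the users kept do no better than the arm average. If they do better, as in step 2, rejection becomes more likely: 66% v 40% with 75 v 107 participants gives about 94% uncorrected. Steps 2 and 3 are alternative scenarios and should not be added together.

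**The case against.** The choice is deliberate and disclosed. The article gives its reason, plans intention-to-treat on the same data so that a discrepancy would be visible, and adjusts for baseline measurement, age and sex. This is fair, but it does not decide which result leads, and the adjustment does not reach motivation.

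Two stronger readings are tempting, and the article supports neither.

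- **That the comparison is biased toward OPEN.** The article does not define the per-protocol set. It gives no usage threshold and never says that website use decides membership; website statistics are listed beside adverse events as things to track. Exclusions for missing outcomes or eligibility breaches could occur in both arms. The definition may properly sit in the full protocol or analysis plan, so its absence here is not a fault. The bias is a plausible risk whose size rests on assumed rates.
- **That the trial lacks its stated 80% power.** The figure reproduces exactly, and power drops below it only if exclusions go beyond the 15% attrition. If the set amounts to completers, the allowance covers it. A usage rule that keeps the more active participants would also raise the chance of rejection, so a power loss cannot be presented as a consequence of the same mechanism.

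The objection leaves the ordering of the two analyses untouched.

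**Conclusion.** The point holds for the choice of primary analysis. The article fixes per-protocol as the main analysis of a superiority hypothesis and justifies it by an aim that does not restore the randomised comparison.

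The direction and size of any bias are conditional. If membership depends on website use, exclusions fall on OPEN alone and would plausibly favour it. Under no true effect with 40% active, excluding 20% of OPEN completers of whom 20% are active gives 5 points and about 11% rejection (8% corrected); the effect is nil if those excluded are as active as the rest. The sample size is sound for 15% attrition and simply makes no provision for further per-protocol exclusions.

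**What to change.** Make the analysis of all randomised participants, as allocated, the primary analysis: logistic regression of 6-month status adjusted for baseline measurement, age and sex. Attach the 80% power statement to it; 252 participants need not change. Report the per-protocol analysis as supportive, with its set defined in advance, including whether website use counts and at what level. How missing outcomes are handled can be left to the analysis plan.

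Both analyses are already planned, so this is a wording amendment. The downside is that non-users dilute the headline estimate. The 60% planning rate is worded for the whole intervention group, so it already describes the all-allocated comparison. If it was meant for users only, the dilution should be acknowledged: with an assumed 20% of non-users active at 40%, the arm rate would be 0.80·0.60 + 0.20·0.40 = 56%, and uncorrected power at 107 per arm about 65%.

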## Introduction

### Background

Arthritis is the most common cause of severe chronic pain and disability [1,2], affecting about 4.6 million Canadians (aged 15 or older) and projected to affect 7 million by 2031 [2]. It is estimated that the majority of these people are affected by osteoarthritis (OA) [3]. Being physically active has been shown to reduce pain, improve quality of life [4-6], and have the potential to slow the progression of joint damage [7]. However, the gap between the *knowledge* about OA management and the *action* of being physically active is extremely large.

Sedentary lifestyle and obesity are predictors of poor health outcomes in people with OA [8-10]. Recent guidelines by the OA Research Society International (OARSI) specifically recommend the use of aerobic, muscle strengthening, and water-based exercises, as well as weight reduction as first line management of knee OA [11], but the majority of people with OA are physically inactive. In 2002, the Arthritis Foundation developed 22 indicators to assess the quality of care in OA [12-14]. When the indicators were applied to a community-based sample in Ontario, 40.1% of people with OA who had no contraindication to exercise had tried exercise [15]. A survey of 1713 people with OA in British Columbia, Canada found that although 79% reported spending time “walking for exercise in the past week”, the majority walked less than one hour per week [16].

Several factors are associated with low participation in physical activities in people with arthritis, some of which are related to the disease (eg, higher levels of pain and fatigue [17-19]), sociodemographics (eg, lower education [20] and income [21]), the person (eg, other commitments, lack of time and motivation [17], doubts about the effectiveness of exercise [19]), and other enabling factors (eg, access to transportation [18], weather [17,18]). People who are newly diagnosed with knee OA tend to have mild pain, stiffness, and functional disability [22]. For these patients, disease-related factors may be a less important barrier to engaging in physical activities. It should be noted that factors associated with physical activity participation were often studied without an overall explanatory framework, making it challenging to develop interventions that work equally well for people with different needs.

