### Adapting Knowledge to the User’s Context: Theory-Informed Lifestyle Interventions

In health promotion, the Theory of Planned Behavior (TPB) has been used extensively to understand and predict health-related/lifestyle change behavior [23]. TPB posits that the adoption of a health *behavior* is driven by the person’s *intention* and *perceived behavioral control (PBC)* [24]. The latter represents the perceived skills/ability, resources, and opportunities of performing the behavior [25]. Furthermore, the strength of *intention* is determined by PBC, the *attitudes* toward the behavior (ie, affective attitude—enjoyment, pleasure evaluations about the behavior; and instrumental attitude—benefit, utility evaluations about performing the behavior) and *subjective norm* (eg, the perception of how others view the behavior and the importance of these views to the person). In a metaanalysis, Hagger et al [26] reported that intention and PBC accounted for about 30% of the variance in physical activity *behaviors*, while attitude and PBC accounted for about 40% of the variance in *intention*. A 2009 metaanalysis by Rhodes found that interventions targeting affective judgement constructs such as affective attitude (eg, enjoyment, pleasure) were effective for predicting intention and physical activity behaviors above the instrumental attitude construct [27].

Although the TPB has not yet been used in the study of physical activity in people with early OA, it has been applied in comparable populations, including older adults [28], those with painful intermittent claudication [29], and those who are obese [30], to inform the development of interventions for improving physical activity. For example, Godin observed that in people with a body mass index (BMI) ≥30, PBC, past behavior, and anticipated regret (ie, the perceived feeling of regret if the behavior is not performed) substantially improved the predictive power of intention, explaining 59% of the variance [30]. Another study examining social cognitive constructs in people awaiting joint replacement surgery for end-stage OA found that pain was a predictor of pre-operative physical activity [31]. Hence, proper monitoring and control of symptoms may be important for people with knee OA during physical activity.

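### The primary model could also adjust for baseline intention and perceived behavioral control, which are already collected before randomisation; this is a cheap gain in efficiency, not the repair of an error

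*Protocol article*

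**What the plan says.** Under Sample Size and Data Analysis, meeting the activity recommendation (yes/no) "will be analyzed in a logistic regression model after adjusting for the baseline measurement, age, and sex". The Abstract gives the same three covariates, so this is a fixed choice and not a detail left open.

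The section on adapting knowledge to the user's context presents the Theory of Planned Behavior (TPB), in which intention and PBC drive behavior. It cites a meta-analysis in which "intention and PBC accounted for about 30% of the variance in physical activity" behaviors. The Background lists several factors linked to low activity, among them "higher levels of pain and fatigue", and also motivation. Age and sex are not on that list.

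On data collection, the Randomized Controlled Trial section says of the TPB questionnaire: "It consists of 16 items measuring all components of the TPB model". Outcome measures are taken at baseline, 3 months and 6 months, and randomisation follows the baseline measures. The TPB scores therefore exist for each participant before allocation. Their only stated analytic use is in the mediation analysis, as changes from baseline.

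**The concern.** The covariates fixed for the primary comparison do not draw on the predictors that the protocol's own theory puts first. Adjusting a logistic model for baseline variables that truly predict the outcome raises the power of the treatment test. Because the baseline TPB scores precede allocation, using them does not adjust away any effect that OPEN has through later changes in the same constructs.

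Two features of this trial make the point worth raising. First, entry requires less than 150 minutes a week of moderate activity, so the baseline activity term has a restricted range. If it is entered in the same yes/no form as the outcome, it will be close to constant and carry little information; the text does not say which form is meant. Second, the plan waives multiplicity adjustment on the ground that Type II error is its greater worry. A plan with that priority has reason to use predictors it already holds. At stake is some precision in the primary contrast, not its validity.

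**Working it through.** **Inputs from Sample Size and Data Analysis.** Control rate: "40% of residents from British Columbia in Canada (N=194, mean age=62 years) started to exercise". Intervention rate: "60% of the intervention group will meet or exceed the recommended level of physical activity at follow-up". Target: "80% power to detect a difference of 20% in physical activity rates between groups and alpha level of .05". Dropout: "Taking into account a 15% loss to attrition over 6 months". Stated size: 252, or 126 per group. Sidedness is not stated; two-sided is taken because it reproduces the figure.

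**Step 1: reproduce the sample size.** With p1 = 0.4, p2 = 0.6, mean 0.5 and difference d = 0.2:

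n = [1.96·√(2·0.5·0.5) + 0.8416·√(0.4·0.6 + 0.6·0.4)]² / 0.2² = (1.3859 + 0.5831)² / 0.04 = 96.9 per arm.

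With continuity correction: n' = (n/4)·[1 + √(1 + 4/(n·d))]² = 24.23 × (1 + √1.2064)² = 106.7, so 107 per arm. Then 107/0.85 = 125.9, so 126 per arm and 252 in total, as stated. Without the correction the total would be 230. The calculation takes no credit for covariates.

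**Step 2: power of the plan as sized.** By the uncorrected normal formula at 107 completers per arm:

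z = (0.2·√107 − 1.96·√0.5) / √0.48 = (2.0688 − 1.3859) / 0.6928 = 0.986, which gives power of 83.8%. The 80% target is met.

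**Step 3: what the extra scores could add.** Simulation with 3,000 trials per setting and 107 per arm. Outcomes came from a logistic model whose intercepts were set so that the marginal rates stayed at 40% and 60%. Predictor strength was set on the latent scale: predictor variance = R²/(1 − R²) × π²/3, where R² is the total explained by the baseline term and the added score. The planned model had arm, age, sex and a baseline term. The extended model added one score carrying the stated R² and two pure-noise covariates, which is one parameter more than the fix below needs. Entries are power of the Wald test for treatment, planned → extended:

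| R² of added score | Baseline term uninformative | Baseline term explains 15% |
|---|---|---|
| 0 | 83.3% → 82.7% | 88.4% → 88.4% |
| 0.05 | 83.6% → 84.5% | 87.6% → 89.0% |
| 0.10 | 83.8% → 86.7% | 85.9% → 88.2% |
| 0.20 | 84.3% → 89.0% | 86.7% → 91.9% |
| 0.30 | 84.1% → 91.6% | 86.7% → 94.6% |

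Monte Carlo error is about √(0.84 × 0.16/3000) = 0.7 points. The gains are nil at R² = 0, about 1 to 3 points at 0.05-0.10, about 5 at 0.20, and about 7.5 to 8 at 0.30.

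**Step 4: cross-check.** A second simulation (4,000 trials per setting, latent-normal outcome, comparator with arm, age and sex only) gave 84.8%, 86.2% and 90.3% with the score at R² = 0.05, 0.10 and 0.30, against about 84% without it. That is about 6 points at 0.30, so the two simulations together give 6 to 8. The variance of the risk difference fell by factors of 1.02, 1.06 and 1.21. Under no effect at R² = 0.30, the rejection rate was 4.8% without the score and 5.6% with it. The standard error is √(0.05 × 0.95/4000) = 0.34 points, so neither is clearly away from 5%.

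**Step 5: room in the model.** Expected events are 107 × 0.4 + 107 × 0.6 = 107 of 214. Two further covariates bring the model to six terms (arm, baseline, age, sex, intention, PBC), about 107/6 = 18 events per term.

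**The case against.** The strongest reply is that nothing here is wrong. The covariate set is short, prespecified and the same in the Abstract and the analysis section. The sample size reproduces, and the planned model exceeds its power target. All of that stands, and it is why this is offered as an improvement.

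A reader might infer more in three ways, and the document supports none of them.

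- **That the plan throws away a known amount of power, set by the 30% figure.** That figure is for intention and PBC together. It is not stated to be net of past behavior, to hold over a 6-month lag, or to come from people with OA. The same section says the TPB has not yet been applied to activity in early OA. OPEN is also designed to change PBC, so how far baseline scores carry through to 6 months is uncertain. The 30% row is therefore an upper bound without direct support, and the gain could be zero.
- **That knee pain belongs in the model on the same footing.** The Background does list pain, but it goes on to say that disease-related factors may matter less in newly diagnosed people, who have mild symptoms and are the population of this trial. The other pain result cited comes from people awaiting joint replacement. Pain is at most optional.
- **That the change is free.** With more predictive covariates, the odds ratio is more conditional and moves further from the marginal 40% versus 60% contrast used for sizing. This is a real though small downside, and reporting on the probability scale deals with it.

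What survives is that the two scores are collected before allocation, are central to the protocol's own theory, and cost little to use. The objections limit the size of the gain; they do not remove the reason to seek it.

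**Conclusion.** The primary model is valid and adequately powered as planned. Adding baseline intention and PBC is a cheap gain in efficiency: about 1 to 3 points of power if they explain 5-10% of latent activity beyond the baseline term, about 6 to 8 points at the unsupported upper bound of 30%, and none if they add nothing. The smaller range is the more cautious one to plan on, given the restricted entry range and the 6-month lag.

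These figures assume rates of 40% and 60%, a two-sided 5% test and 107 analysed per arm, which allows for the stated attrition only. Every R² value, including the 15% given to the baseline term, is an assumption. The point does not depend on how the baseline term is coded, since a gain appears whether that term is informative or not.

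**What to change.** Before any unblinded analysis, add one sentence to the primary analysis: the 6-month logistic model adjusts for the baseline measurement, age, sex, baseline TPB intention and baseline TPB PBC, the last two as continuous scores. Only baseline values should enter; changes in these scores stay in the mediation analysis. Report standardised proportions per arm or a risk difference alongside the odds ratio, so that the result can be read against the 40% and 60% used for sizing. KOOS pain may be added if the team wishes, but it should be decided at the same time and not after seeing results.

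The cost is two extra parameters, a more conditional odds ratio and a short addition to the reporting. No new data, visits or participants are needed, and the sample size stays as it is.
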